## Abstract

**Background:**

Monkeypox is a viral zoonotic disease commonly reported in humans in parts of Central and West Africa. This protocol is for an Expanded Access Programme (EAP) to be implemented in the Central African Republic, where Clade I monkeypox virus diseases is primarily responsible for most monkeypox infections. The objective of the programme is to provide patients with confirmed monkeypox with access to tecovirimat, a novel antiviral targeting orthopoxviruses, and collect data on clinical and virological outcomes of patients to inform future research.

**Methods:**

The study will be conducted at participating hospitals in the Central African Republic. All patients who provide informed consent to enrol in the programme will receive tecovirimat. Patients will remain in hospital for the duration of treatment. Data on clinical signs and symptoms will be collected every day while the patient is hospitalised. Blood, throat and lesion samples will be collected at baseline and then on days 4, 8, 14 and 28. Patient outcomes will be assessed on Day 14 –end of treatment–and at Day 28. Adverse event and serious adverse event data will be collected from the point of consent until Day 28.

**Discussion:**

This EAP is the first protocolised treatment programme in Clade I MPXV. The data generated under this protocol aims to describe the use of tecovirimat for Clade I disease in a monkeypox endemic region of Central Africa. It is hoped that this data can inform the definition of outcome measures used in future research and contribute to the academic literature around the use of tecovirimat for the treatment of monkeypox. The EAP also aims to bolster research capacity in the region in order for robust randomised controlled trials to take place for monkeypox and other diseases.

**Trial registration:**

**{2a & 2b}**: ISRCTN43307947.

## Background

### Background and rationale {6a}

Monkeypox is a viral zoonotic disease commonly reported in humans in parts of Central and West Africa, including the Central African Republic (CAR), the Democratic Republic of Congo (DRC), Republic of Congo, Nigeria, Sierra Leone and Liberia [1]. There are two genetic clades of the monkeypox virus–Clade I has typically circulated in Central Africa and is associated with higher mortality [2], and Clade II in West Africa–as well as a sub-clade, Clade IIb, which was identified as being responsible for the multi-country outbreak of monkeypox in typically non-endemic countries starting in May 2022 [3].

This protocol is for an Expanded Access Programme (EAP) to be implemented in CAR, where Clade I MPXV is primarily responsible for most monkeypox infections (Institut Pasteur de Bangui [Unpublished]). There have been approximately 100 cases of monkeypox reported in CAR since 2000 –primarily in South-Western (Lobaye, Mambere-Kadei, Sanga-Mbaere), and South-Eastern (Mbomou) prefectures [4]. Reports of MPXV in humans in CAR have increased in recent years partly due to improvements in surveillance, but also as a result of the cessation of the smallpox vaccination programme–leading to reduced cross-protection against orthopox viruses–civil unrest and rampant deforestation, which is increasing contact between wildlife and humans [5,6]. In CAR, monkeypox has been reported in patients who have hunted wildlife [5] and is associated with harvesting caterpillars–a seasonal activity which sees individuals and families spend prolonged periods of time in the rainforests, often coming in to contact with bushmeat.

Patients who are diagnosed with monkeypox have limited treatment options. Until recently, supportive care to alleviate monkeypox symptoms–such as lesions, fever, headache, back and muscle aches, and lymphadenopathy–was the only treatment available [7]. However, tecovirimat–a novel antiviral targeting orthopox viruses by inhibiting the formation of the virus envelope, thus preventing its exit from infected cells–has recently been approved in several countries under exceptional circumstances in response to the 2022 multi-country monkeypox outbreak [8]. At the time this EAP was started, tecovirimat was only approved by the United States Food and Drug Administration (FDA) for smallpox under the so-called “animal rule” [9]. In all cases, despite receiving regulatory approval for the treatment of monkeypox, there is limited efficacy and safety data for the use of tecovirimat for monkeypox. Previous clinical data supporting tecovirimat are essentially on safety and tolerability from studies in healthy volunteers; there are only a handful of reports on tecovirimat used to treat patients with confirmed monkeypox infection, none of which are from randomised controlled clinical trials (RCTs) [10–13].

As with many other outbreak-prone infectious diseases, initiating an RCT for monkeypox poses several challenges. Firstly, monkeypox is reported sporadically over widespread geographical areas in rural parts of CAR, and other endemic regions, with limited healthcare infrastructure and poor transport links, making the implementation of a clinical trial challenging. Monkeypox is also reported in relatively small numbers of patients [4] and, while the case fatality rate in Clade I MPXV is around 10% (Institut Pasteur de Bangui [Unpublished]), mortality is too low for it to be used as the primary endpoint in any clinical trial–the overall required sample size would be unfeasibly high for an effect to be detected between treatment groups. Alternative endpoints therefore need to be identified, which is complicated by the diversity of symptoms experienced by patients with monkeypox and lack of clinical and virological data on patient outcomes [14].

While conducting an RCT may not be an option now in CAR, conducting an EAP of tecovirimat to treatment monkeypox in CAR therefore has several benefits: the EAP will provide patients with access to a potentially life-saving treatment that would not otherwise be available; it will allow the collection of data on signs and symptoms, and clinical and virological outcomes of patients under a standardised protocol; and finally build research capacity to conduct future clinical research studies, including RCTs using an Investigational Medicinal Product (IMP).

## Methods

### Objectives {7}

The primary objective of this EAP is to provide access to tecovirimat to patients with monkeypox who have no comparable or satisfactory therapeutic alternative and cannot participate in a clinical trial.

The secondary objective of this study is to describe the clinical, virological and safety outcomes of patients with monkeypox virus disease.

### Methods/Design {8}

This protocol has been written according to the SPIRIT guideline (**S1 Text**).

This is an Expanded Access Programme (EAP) providing treatment for monkeypox virus disease to patients with PCR confirmed monkeypox in CAR.

All patients who sign the informed consent form (**S2 Text**) and enrol in the programme will receive tecovirimat–this is not a randomised study.

Data are collected on signs and symptoms and treatment administration every day while patients are hospitalised and receiving treatment. Data on patient outcomes are collected on D14 and D28. Adverse events (AEs) and Serious Adverse Events (SAEs) are collected from the point of consent until D28.

Blood, throat, and lesion samples are collected whenever possible at enrolment, D4, D8, D14 and D28. An additional blood, throat and lesion sample will be collected at D21 if patients test positive on any sample at D14.

While the primary objective of this EAP is to provide patients with access to treatment, the data collected in this study will be used to evaluate the outcomes of patients who receive tecovirimat. These data will contribute to the academic literature about the use of tecovirimat for the treatment of Clade I monkeypox.

This protocol also aims to build clinical research capacity in CAR.

### Ethics approval and consent to participate {24}

Ethical approval was obtained from the Oxford Tropical Research Ethics Committee (OxTREC) (ref: 1–20) and the University of Bangui Ethics Committee before the first patient was enrolled in the programme. All patients provide written informed consent before enrolment.

### Trial registration {2a & 2b}

This EAP is registered on the ISRCTN registry with the following identifier: ISRCTN43307947.

### Programme setting {9}

This EAP is taking place in participating hospitals in the Central African Republic.

### Eligibility criteria {10}

#### Inclusion criteria

This programme is enrolling male and female patients who meet the following criteria:

Confirmation of monkeypox virus disease by PCR, or patients who are being managed as a presumptive case pending laboratory confirmation*Weight ≥13 kgWilling to provide informed consent to enrol in the programme

*A blood, pharyngeal, and lesion swab are taken for confirmation by qPCR positivity for monkeypox virus DNA, but enrolment will not await laboratory confirmation if there is high clinical suspicion of disease. A patient who is a presumptive case and subsequently tests negative for MPXV will exit the study. A positive PCR result on any of the samples constitutes evidence of MPXV infection.

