## Interventions

### Explanation for the choice of comparators {6b}

This is a non-comparative EAP. All patients enrolled in the study will receive tecovirimat according to the Investigator’s Brochure (IB).

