## Assignment of interventions: Allocation

### Sequence generation {16a}

This is not a clinical trial and patients are not randomised to treatment. All enrolled patients receive tecovirimat.

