## Statistical methods

### Statistical methods for analysing outcomes {20a}

Clinical and virological outcomes will be assessed at D14 and D28 for all patients and then at D21 for patients who are still positive at D14. Due to the non-comparative nature of the study and small number of patients anticipated to be enrolled in the study, only descriptive analyses of clinical and virological outcomes will be presented in the final analysis; no inferential statistical testing will be performed to evaluate changes in outcomes.

To describe the cohort, patient demographics will be described in terms of the ratio of males to females in the cohort, and the median age and range in years. The number and percentage of patients with comorbidities at inclusion, including malaria and human immunodeficiency virus, infection will be presented, along with the median interval in days from symptom onset to initiation of treatment.

Signs and symptoms will be reported in terms of the number and percentage of patients presenting with the symptom, which are assessed at each visit and will be reported at baseline and post-baseline timepoint. Signs and symptoms will be reported for all patients both from a pre-defined list included in the CRF and any additional AEs that may have arisen from the point of consent until D28. The signs and symptom reporting will also include the number and percentage of patients with lesions–subcategorised in to active lesions, crusts and resolved lesions–their distribution and number of lesions observed.

Treatment adherence will be reported in terms of the number and percentage of patients who completed a full course of treatment. Non-adherence will be reported in a supplementary narrative explanation.

Patient outcomes will be reported as the number and percentage of participants who meet the clinical criteria described in Table 3 at D14 and D28, along with the number and percentage of participants who tested positive for mpox virus on D4, D8, D14, D21 and D28.

Narrative summaries of SAEs will be presented alongside a tabulated summary of the number and percentage of patients who experience each SAE, for which event names will be MedDRA coded. For each SAE the grade and outcome will be reported.

Full details of the planned analyses can be found in the Statistical Analysis Plan.

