### Adverse event reporting and harms {22}

Details of Adverse Events (AEs) and Serious Adverse Events (SAEs) are collected from the point of consent until the Day 28 visit.

AEs and SAEs are defined and reported according to the WHO Collaborative Centre definitions incorporated in to the European Medicines Agency Guideline for Good Clinical Practice E6 [16].

AEs are recorded directly on the standardised paper CRF and transferred on to the RedCap database by the data manager. The data collected for all AEs includes the event name, event grade, start and end dates and outcome.

SAEs require expedited reporting to the Sponsor. SAEs are defined as any untoward medical occurrence that:

results in deathis life-threateningrequires inpatient hospitalisation or prolongation of existing hospitalisationresults in persistent or significant disability/incapacityconsists of a congenital anomaly or birth defect.

Other ‘important medical events’ may also be considered a serious adverse event when, based upon appropriate medical judgement, the event may jeopardise the participant and may require medical or surgical intervention to prevent one of the outcomes listed above.

All SAEs should be reported to the Sponsor and PI on the standardised SAE report form within 24 hours of the site-based programme team becoming aware of the event.

The treating clinician (the PI or Co-I) will provide a causality assessment of the relationship between the event and tecovirimat. The relationship will be evaluated as either: 1) definitely related; 2) probably related; 3) possibly related; 4) unlikely to be related; 5) not related. The Medical Monitor will provide a second causality assessment using the same scale. Events will be considered as “related” to tecovirimat if either causality assessment is returned as “definitely”, “probably”, or “possibly” related. These events will be considered as Serious Adverse Reactions (SARs). Events that are considered to be “unlikely” or “not related” will remain as SAEs.

The Medical Monitor will also assess the expectedness of the event against the Investigator’s Brochure (IB). Related events that are unexpected will be considered SUSARs.

All SAEs must be reported to the ethics committee of the University of Bangui within 72h of the programme team becoming aware of the event.

All SARs must be reported to the Oxford Tropical Medicine Ethics Committee (OxTREC) within 7 working days.

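### Presumptive cases who test PCR-negative exit the study after enrolment, with no provision to continue the adverse-event collection promised to Day 28 for everyone enrolled

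*Protocol article*

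**What the plan says.** All references are to the protocol article.

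- **Entry before confirmation.** The footnote to the inclusion criteria (Eligibility criteria {10}) says that "enrolment will not await laboratory confirmation if there is high clinical suspicion of disease".
- **Exit on a negative result.** The same footnote continues: "A patient who is a presumptive case and subsequently tests negative for MPXV will exit the study". It gives no timing for the exit and says nothing about safety follow-up afterwards.
- **Exposure.** Explanation for the choice of comparators {6b} says "All patients enrolled in the study will receive tecovirimat". Sequence generation {16a} repeats it: "All enrolled patients receive tecovirimat".
- **Safety window.** Methods/Design {8} says "Adverse events (AEs) and Serious Adverse Events (SAEs) are collected from the point of consent until D28". Adverse event reporting and harms {22} says that details of these events "are collected from the point of consent until the Day 28 visit". Table 3 (Outcomes {12}) counts the safety outcomes over the 28 days after enrolment.
- **Population.** Methods/Design {8} describes the programme as "providing treatment for monkeypox virus disease to patients with PCR confirmed monkeypox in CAR", which leaves out the presumptive cases that the eligibility section admits.

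**The concern.** A presumptive case who turns out PCR-negative falls under two rules that cannot both be followed. The eligibility footnote ends that patient's participation. The design, outcomes and harms sections keep every consented patient under safety observation to Day 28.

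If the exit rule prevails, a late event in a patient who took the drug is never recorded. It would then be absent from the counts of SAEs, serious adverse reactions and SUSARs. It might also never reach the medical monitor, who is the main safety oversight here because no data monitoring committee has been convened ({21a}), or the ethics committees to which {22} requires reports.

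This concerns conduct, not analysis. A statistical analysis plan can choose a denominator, but it cannot recover events that were not collected.

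**Working it through.** The protocol gives no sample size calculation, power or error rate bearing on this point, so there is no figure to reproduce. The check is a comparison of the sections.

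**Step 1. Can a patient be enrolled and later found negative?** Yes. The eligibility footnote provides for both.

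**Step 2. Has that patient been exposed?** The text says that enrolment, not explicitly the first dose, precedes the result. Three things make exposure the natural reading:
- {6b} and {16a} give the drug to everyone enrolled.
- No section makes dosing wait for PCR.
- Samples go to the national reference laboratory in Bangui ({18a}), not to a laboratory at the treating hospital.

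If dosing did wait, the statements in {6b} and {16a} would be untrue for those who exit. The text needs correcting on either reading.

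**Step 3. Does safety collection continue after exit?** No section says so. Ending collection is the plain meaning of leaving a study.

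| Topic | Eligibility {10} | Other sections |
|---|---|---|
| Duration of AE/SAE collection | Participation ends after a negative PCR; no safety provision | Consent to Day 28 ({8}, {22}); 28 days from enrolment (Table 3) |
| Who is treated | Confirmed and presumptive cases | PCR-confirmed cases ({8}) |
| Exception for PCR-negative patients | Exit rule only | None in {8}, {12} or {22} |

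**Step 4. What is lost?** Events between consent and exit are collected under {8} and {22}. Only events from exit to Day 28 are at risk. The missing-data section {20c} relies on denominators and narrative explanation and does not mention this group.

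**Step 5. How many patients?** This cannot be derived. The documents give neither the share of presumptive cases that test negative nor the time to a result. As an illustration only, take the 100 patients for whom ethical approval was obtained ({14}) and assume that 0% to 30% exit and contribute nothing. For an event never observed in n patients, the exact two-sided 95% upper limit is 1 − 0.025^(1/n):

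| Assumed exit share | n | Upper limit |
|---|---|---|
| 0% | 100 | 1 − 0.025^(1/100) = 3.6% |
| 10% | 90 | 1 − 0.025^(1/90) = 4.0% |
| 20% | 80 | 1 − 0.025^(1/80) = 4.5% |
| 30% | 70 | 1 − 0.025^(1/70) = 5.1% |

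The assumption overstates the loss, since events before exit are kept, and 100 is an approved number, not a forecast of enrolment. Even so, the effect on precision is modest. What matters is that individual events in exposed patients may go unrecorded.

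**The case against.** The strongest reply starts from Objectives {7}, which limits the secondary objective to outcomes, including safety, in patients who have the disease. A PCR-negative patient is outside that group, so ending participation fits the aim. The Background says that safety evidence is thin for the drug in monkeypox and that earlier data come mainly from healthy volunteers. Patients without the disease would add little to that gap. This has force for the clinical and virological outcomes. It does not remove the conflict, because the safety windows and the reporting duties in {22} are not restricted to confirmed patients.

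A second reply is that exposure may be short, since the Discussion says samples reach the laboratory with little delay. That is plausible, but no turnaround time is stated, and the Day 28 window applies however many doses were taken.

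A third reply is that analysis sets belong in the statistical analysis plan, which is not shown. This stands. The protocol says "Treatment adherence will be reported in terms of the number and percentage of patients who completed a full course of treatment", and whether exited patients enter that percentage is properly left to the plan. So is the formal definition of a safety set.

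On the population wording, {8} is a one-sentence summary, and removing those who test negative does leave a PCR-confirmed cohort. That part is a wording correction and no more.

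A reader might also infer that exposed patients leave immediately, that their data are discarded, or that a substantial fraction of the cohort is lost. The documents support none of these. The exit has no stated timing, nothing says that collected data are deleted, and the fraction is unknown.

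**Conclusion.** The concern holds in a limited form. The eligibility footnote conflicts with the unqualified Day 28 safety window in {8}, Table 3 and {22}. As written, AEs and SAEs arising after exit in tecovirimat-exposed, PCR-negative patients would go uncollected and be missing from the safety counts.

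This rests on two inferences, both natural but neither stated: that dosing can begin before the PCR result, and that leaving the study ends event collection. The number affected cannot be determined from the documents. The precision loss in the illustration is modest and, in a descriptive programme, is not shown to change any conclusion. The point is still worth correcting, because uncollected safety data cannot be recovered at the analysis stage.

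**What to change.** Reconcile the eligibility footnote with {8}, Table 3 and {22}:

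- State that a presumptive case who tests PCR-negative leaves the clinical and virological outcome analyses, but that any patient who received at least one dose remains in AE and SAE collection to Day 28 and is counted in the safety reporting.
- Report the number of patients treated but not confirmed.
- Amend the description of the population in {8} so that it covers presumptive cases as well as PCR-confirmed ones.

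This changes data collection and reporting only. It takes no position on the treatment of PCR-negative patients.

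The cost is a short amendment, which {25} requires the ethics committees to approve, and a Day 28 safety contact for the patients concerned.

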#### Exclusion criteria

Patients will be excluded from the study if they meet any of the below criteria:

Co-administration of repaglinideCo-administration of midazolamGalactose intolerance, total lactase deficiency or glucose-galactose malabsorption

### Who will take informed consent? {26a}

All patients who meet the eligibility criteria are informed about the programme by the Principal Investigator (PI) or Co-Investigator (Co-I) in CAR. Interested patients are given the Patient Information Sheet (PIS) (S2 Text), which is available in either French or Sango. Patients will be given sufficient time to read the (PIS), consider their participation and discuss the programme with the PI or Co-I.

The PI and Co-I will obtain written informed consent from all patients (or their legal representatives) enrolled in the programme before commencing any study-specific procedures.

Adult patients are defined as those being 18 years old and above.

If an adult patient does not have capacity to provide informed consent, written advice will be sought by the PI or Co-I from a close relative who attends the health centre with the patient (a personal consultee) or an appropriate independent individual (nominated consultee). If the patient later regains capacity, they will be provided with the PIS and asked to consider whether they wish to continue participating in the programme.

For all children aged up to 17 years, key elements of the programme will be explained by the PI or Co-I in a manner that is appropriate for the child’s age and maturity. Verbal assent will be sought from the child and written informed consent will be sought from a parent or legal representative.

